### Sample size calculation

The baseline screening rates in our sample size calculation rates are obtained from our feasibility studies and local data. The overall sample size was chosen to ensure sufficient power to detect clinically meaningful effects associated with a 15% point increase in proportion of additional screening done in the home-based arm versus primary care arm using two-sided test for differences in proportion. Although we plan to conduct intention-to-treat analyses, in which all women lost to follow-up will be considered “unscreened,” we will also conduct analyses with lost to follow-up participants excluded. For these analyses, we need to account for attrition (21% in our previous study). In addition, in our subgroup analysis where we look at each individual test, we set alpha at 1.25% instead of 5% to account for multiple testing. Even with a 25% attrition rate, a proposed total sample size of 900 participants (450 per arm and 150 per site) will give us over 95% power for our primary outcome and 90% power for the subgroup analysis.

### Fidelity

Intervention fidelity is assessed via weekly review of CHW encounter logs, which are documented every time the CHW has contact or attempts contact with a participant. Any issues or inconsistencies elucidated by this regular review are addressed and resolved at team meetings. In addition, we will assess participant knowledge of the four target conditions and screening following the intervention, which can help assess if disease education was administered effectively by the CHWs.

### Withdrawal of participants from study

Participants may request to be withdrawn from the study at any time by contacting the CHE. If a participant elects to withdraw, their reason for withdrawal will be recorded and their study data will be deleted.

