### Recruitment

Trial recruitment occurs via convenience sampling at community-based locations such as markets, churches, botanicas, and health clinics, as well as via the social networks of our CHWs and community partners. The CHWs approach potentially eligible individuals, screen for eligibility, and explain the study. Eligible and interested individuals are asked to provide their contact information, and CHWs will try up to ten times to contact eligible individuals to schedule them for informed consent and study intake. Participants who agree to participate complete a 30‑minute intake interview in their home or location of their preference. The CHWs work closely with our two bilingual research associates (RAs) to set up these visits during which informed consent and study intake occur. Our RAs are master’s level highly trained research professionals. Upon completion of the intake interview, participants are randomized into one of two interventions.

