### Allocation of trial interventions

Following the study intake, participants are randomized to one of the two study interventions by the study biostatistician, using REDCap’s randomization module. The module randomizes study participants electronically, and randomizes within study sites to account for nesting. The CHWs are notified via email of the assignment of participants following the randomization, and will follow up with participants within a week to inform them of their assignment, and to schedule a home visit (if the participant is in the home-based testing arm). Notably, while participants and CHWs are aware of group assignment, the community health educator (CHE), who collects study outcome data, is blinded to participant assignment.

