### Outcome measures

#### Primary outcome

Our primary study outcome measure will be proportion of participants fully up to date on all their needed screenings for these four health conditions (three for men) at 6 months post-study enrollment. We will conduct intention-to-treat analysis based on study allocation. This outcome will be a binary (yes/no) variable. Participants in either group lost to follow-up at 6 months will be assumed not to have been screened in intention-to-treat analyses.

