### Statistical analysis

Prior to any analysis, data screening for accuracy will be conducted and will focus on several aspects. We will determine the amount, pattern, and randomness of missing data. Outliers will be identified observations that appear to be very high or very low, and decide how to proceed based on the presumed cause. We will also identify inconsistencies within a single variable and between variables. As there are various types of measurements, we will use various descriptive statistics to visualize the study data with the appropriate graphical displays. Initially, we will perform an explanatory data analysis; visually via graphics/plots such as scatter and box-whisker plots and numerically by descriptive statistics such as range, median, means, standard deviations for measurements taken on a continuous scale, and percentages, various types of cross-tabulations for measurements taken on a categorical scale. Corresponding confidence intervals for means and proportions will also be calculated. To have a better understanding of the relationships among different study measurements, parametric or non-parametric correlation coefficients, bivariate, and multidimensional cross-tabulations, scatter and box-whisker plots will be constructed. Prior to analyses, baseline differences of key covariates from the PC and HBT arm will be examined with respect to our primary and secondary outcomes, particularly those related to race, ethnicity, SES and education. We will also examine differences on key variables between subjects who completed the study and those lost to follow-up. Our primary analysis will consist of chi-squared testing for the differences in proportions among the PC versus HBT study arms. Several univariate and multivariate logistic regression models will be used to calculate odds ratios and corresponding 95% confidence intervals for exploring the result of the screening and the relation to various types of key study variables in addition to study arms. Two-way interaction terms between for various study variables and the study arms may need to be included in the models. Transformations of the continuous data in order to meet statistical assumptions may be undertaken if indicated. Type-1 error will be set to 5% (α = 0.05) for calculating confidence intervals and testing various hypotheses for the primary outcome. Adjustment of type-I error for multiple comparisons will be performed by controlling the family-wise type-I error rate at the 0.05 level. Standard diagnostic tools will be used to assess any model fit. All statistical analyses will be carried out using SAS® v9.4 for Windows (SAS Institute, Cary, NC, USA) and/or R-project for Windows.

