#### Adverse events

The study team will collect information and monitor any adverse events, including any injury incurred as a result of self-testing. If an adverse event occurs, participants will be immediately referred to appropriate medical care, and the study team will report the event to the principal investigators (PIs) and the IRB. Information regarding adverse events will be recorded in REDCap.

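### Deleting the study data of participants who withdraw may remove randomised people from an analysis declared intention-to-treat; the withdrawal rule and the primary-outcome rule need to be reconciled.

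*Protocol article*

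**What the plan says.** The rules come from different sections of the protocol article.

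- *Withdrawal of participants from study*: "Participants may request to be withdrawn from the study at any time by contacting the CHE". If they do, "their reason for withdrawal will be recorded and their study data will be deleted".
- *Recruitment*: "Upon completion of the intake interview, participants are randomized into one of two interventions". Anyone who withdraws after that point has been randomised.
- *Primary outcome*: "We will conduct intention-to-treat analysis based on study allocation". On missing outcomes: "Participants in either group lost to follow-up at 6 months will be assumed not to have been screened in intention-to-treat analyses". Withdrawal is not named there. *Sample size calculation* repeats the rule for losses and also does not name withdrawal.
- *Statistical analysis*: "Our primary analysis will consist of chi-squared testing for the differences in proportions among the PC versus HBT study arms". That section also plans a comparison of completers with those lost to follow-up.
- *Adverse events*: "Information regarding adverse events will be recorded in REDCap". The same section has events reported to the principal investigators and the IRB.

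**The concern.** Two participants who leave without a 6-month interview can be treated in opposite ways. One who goes silent stays in the denominator as a failure. One who tells the study that they are leaving has their data deleted and may vanish from numerator and denominator alike. An analysis that loses randomised people in this way is not intention-to-treat.

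Assignment is open: "participants and CHWs are aware of group assignment". The arms also ask different things of people: visits to a clinic or other service in Group 1, and finger-stick, self-sampling and stool kits in Group 2. Withdrawal could therefore depend on arm and be related to outcome, which is when deletion biases the comparison. Withdrawn people would also be missing from the completer-versus-lost comparison, and their REDCap adverse-event entry might be deleted.

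The article is explicit about deletion, so this is a stated rule and not a detail left to an analysis plan. An analysis plan could not restore erased records.

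**Working it through.** **The plan's own figure.** *Sample size calculation* gives 900 participants (450 per arm), a 15-point difference, 25% attrition, and power over 95% for the primary outcome and 90% for the individual tests at alpha 1.25%. The control rate is not stated, so it was varied from 5% to 80% (assumption). With 450 × 0.75 = 337 per arm (rounded down) and a two-sided normal-approximation test, the lowest power is 97.5% at alpha 5% and 92.1% at alpha 1.25%. The stated power holds. The issue is bias.

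**Formula.** In one arm let p be the share of all randomised people who meet the outcome, w the share who withdraw and are deleted, and r the success rate among those who withdraw. After deletion the observed proportion is

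(p − w·r) / (1 − w),

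so the arm's proportion shifts by w·(p − r) / (1 − w). The shift is upward if r < p, nil if r = p, and downward if r > p. If no withdrawn person meets the outcome (r = 0), the observed proportion is p / (1 − w).

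**No true difference, p = 40% in both arms, r = 0.** All withdrawal shares are assumed, because the article gives none.

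| Withdrawal, arm A / arm B | Arm A | Arm B | Spurious difference |
|---|---|---|---|
| 3% / 6% | 0.40/0.97 = 41.24% | 0.40/0.94 = 42.55% | 1.32 points |
| 5% / 10% | 0.40/0.95 = 42.11% | 0.40/0.90 = 44.44% | 2.34 points |
| 2% / 8% | 0.40/0.98 = 40.82% | 0.40/0.92 = 43.48% | 2.66 points |
| 5% / 5% | 42.11% | 42.11% | 0 |

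In people, the 2% / 8% row is 180 screened of 441 against 180 of 414, where the declared analysis would have 180 of 450 in each arm.

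**If r is not zero.** With r = 20% (half of p), the 2% / 8% case gives 0.08 × 0.20/0.92 − 0.02 × 0.20/0.98 = 1.74 − 0.41 = 1.33 points, half as much.

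**Effect on the test.** At p = 50% in both arms and r = 0, the chi-squared test at nominal 5% rejects in 7.6% of trials with withdrawal of 2% / 5%, in 13.5% with 5% / 10%, and in 5% when withdrawal is equal.

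**With a true effect.** Equal withdrawal then also shifts the estimate, though only slightly. For 50% versus 65% with 5% withdrawn in each arm, 0.65/0.95 − 0.50/0.95 = 15.8 points instead of 15.0.

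**The case against.** The strongest reply is that counting someone as unscreened needs only their allocation. Allocation is generated in REDCap's randomisation module and emailed to the community health workers, and the reason for withdrawal is kept. The article does not say that the randomisation record is part of the deleted study data, nor that a withdrawn person is not regarded as lost to follow-up. This stands as far as it goes. A reader might infer that withdrawn people are certain to leave the denominator, and the text does not establish that. It does not establish the opposite either, and deletion is the only rule it states.

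Three further limits also stand.

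- A reader might infer that safety information is lost. The withdrawal section does not mention adverse events, and reports to the principal investigators and IRB would remain. At most the REDCap entry goes.
- A reader might infer that deletion always favours the arm with more withdrawals. That holds only if withdrawn people are screened less often than those who stay. In Group 2, HIV and HCV tests are done at the intervention visit, so some people could be tested before they withdraw.
- Arm-dependent formal withdrawal is plausible but not shown to be common. Home tests can be declined without leaving the study, Group 1 has several routes to screening, and simply not responding is easier than asking to withdraw.

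The size is also modest under these assumptions. The standard error of the difference at 40% with 450 per arm is √(2 × 0.40 × 0.60/450) = 3.3 points, which exceeds each spurious difference in the table.

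**Conclusion.** The point holds as an unreconciled conflict between two stated rules. As written, randomised participants who withdraw may be dropped from an analysis that the same article calls intention-to-treat by allocation, and no passage prevents it. Bias in the no-effect case requires that withdrawal differs by arm and is related to outcome. Under the illustrative shares it is 1.3 to 2.7 points against a 15-point target, and it is nil when withdrawal is equal and there is no true effect. The true size and direction are unknown because no withdrawal rate is given.

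A reader might conclude that the primary result is invalid or that the planned power fails. The document supports neither: the stated power reproduces, and few withdrawals would leave little bias. The rule should still be fixed, because it touches the primary comparison, deletion cannot be undone, and the change is cheap.

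**What to change.** Change the withdrawal section along these lines:

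- Withdrawal ends participation, but allocation and data collected up to that point, including adverse events, are kept as far as consent allows.
- Withdrawn participants stay in the randomised denominator of their arm. Screening recorded before withdrawal is used; otherwise they count as unscreened under the primary-outcome rule.
- Withdrawals are reported by arm, with reasons.
- Where a participant requires erasure, or earlier consent promised it, at least the arm-level count is kept so that the person can be included as unscreened, and the departure is stated.

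Screening before withdrawal is more likely to be on record in Group 2, where study staff do or process the tests, than in Group 1, where the outcome rests on self-report at 6 months. A sensitivity analysis that counts every withdrawn person as unscreened would show whether this matters.

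The cost is a wording change through the IRB and no new data collection. With 705 of 900 enrolled by January 2020, data already deleted cannot be restored, and the new rule may not apply to people whose consent promised deletion. For them, arm counts might be recovered from assignment emails or encounter logs, if these survive.

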### Data management

Study data will be collected and stored within the REDCap system, which is a web-based, secure, and HIPAA-compliant research management platform. REDCap fully supports several research processes for patient recruitment and scheduling, participant randomization, data entry and management, as well as data safety monitoring and adverse event reporting. A particular advantage of REDCap is that CHEs are immediately notified if fields are missing and/or if out or range values are entered. However, in case of loss of internet access, backup paper copies are provided, which would then be subsequently entered into REDCap. The data manager regularly screens the REDCap data for quality control, and any issues or inconsistencies are discussed with the CHEs. De-identified data is extracted from REDCap for data analysis.

### Statistical analysis

Prior to any analysis, data screening for accuracy will be conducted and will focus on several aspects. We will determine the amount, pattern, and randomness of missing data. Outliers will be identified observations that appear to be very high or very low, and decide how to proceed based on the presumed cause. We will also identify inconsistencies within a single variable and between variables. As there are various types of measurements, we will use various descriptive statistics to visualize the study data with the appropriate graphical displays. Initially, we will perform an explanatory data analysis; visually via graphics/plots such as scatter and box-whisker plots and numerically by descriptive statistics such as range, median, means, standard deviations for measurements taken on a continuous scale, and percentages, various types of cross-tabulations for measurements taken on a categorical scale. Corresponding confidence intervals for means and proportions will also be calculated. To have a better understanding of the relationships among different study measurements, parametric or non-parametric correlation coefficients, bivariate, and multidimensional cross-tabulations, scatter and box-whisker plots will be constructed. Prior to analyses, baseline differences of key covariates from the PC and HBT arm will be examined with respect to our primary and secondary outcomes, particularly those related to race, ethnicity, SES and education. We will also examine differences on key variables between subjects who completed the study and those lost to follow-up. Our primary analysis will consist of chi-squared testing for the differences in proportions among the PC versus HBT study arms. Several univariate and multivariate logistic regression models will be used to calculate odds ratios and corresponding 95% confidence intervals for exploring the result of the screening and the relation to various types of key study variables in addition to study arms. Two-way interaction terms between for various study variables and the study arms may need to be included in the models. Transformations of the continuous data in order to meet statistical assumptions may be undertaken if indicated. Type-1 error will be set to 5% (α = 0.05) for calculating confidence intervals and testing various hypotheses for the primary outcome. Adjustment of type-I error for multiple comparisons will be performed by controlling the family-wise type-I error rate at the 0.05 level. Standard diagnostic tools will be used to assess any model fit. All statistical analyses will be carried out using SAS® v9.4 for Windows (SAS Institute, Cary, NC, USA) and/or R-project for Windows.

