### Trial procedures 

#### Enrollment visit

During the enrollment visit, the CHE explains the study to the participants, answers participant questions, confirms participant eligibility, and obtains informed consent. Following informed consent, the CHE conducts an intake interview. Based on our experience with respondent fatigue as well as based on the recommendations of our community partners, we try to keep the intake interview to no more than 30 minutes in length. The interview includes questions on sociodemographic characteristics, previous experiences with disease screening for each of our four conditions, condition-specific disease knowledge, health beliefs and access to care. The intake interview (as well as informed consent and all other study measures), have been translated into Spanish and Haitian Creole by certified translators using validated back-translation methods.

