## Discussion

Our project addresses the excess burden of HIV, HCV, CRC, and cervical cancer experienced by Little Haiti, Hialeah, and South Dade, three medically underserved communities within the Miami metropolitan area. Using a CBPR approach, we will determine the effectiveness of navigation to primary care for screening versus CHW-delivered, home-based, multimodality screening among 900 individuals from our target communities. Study findings will allow us to optimize this for disease screening in real-world settings.

There are several study limitations that should be considered. There is only one CHW per community, which impedes our ability to determine whether potential differences in intervention effectiveness by community are due to community or CHW-related factors. We apply regular monitoring and quality control to maximize fidelity among study CHWs. Moreover, the CHW encounter logs may be used to better understand the influence of CHW-related factors on study outcomes. Our results also may not be generalizable outside of our target communities, as the current intervention approaches are heavily tailored based on community partner input. While this approach is a valid method of addressing health disparity within these specific communities, the effectiveness of multi-modality home-based testing would likely need to be re-examined if implemented outside of our target communities. Lastly, our primary outcome is based on self-report. However, self-reported data may overestimate the proportion of persons who obtained the screenings. For participants in the HBT group who choose home testing, we will have objective lab data to validate their self-reported data. However, if participants in the PC group overestimate their screenings, it could bias our results towards the null hypothesis.

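### Participants are randomised within site, but the primary chi-squared test ignores site and the number of overdue tests at entry: valid, but mildly conservative and less precise if these factors are prognostic

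*Protocol article*

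**What the plan says.** - **Allocation.** Under Allocation of trial interventions, the REDCap module "randomizes within study sites to account for nesting". There are three communities, and the Discussion adds: "There is only one CHW per community". Site and CHW are therefore the same factor, and each CHW serves both arms.
- **Primary test.** Under Statistical analysis: "Our primary analysis will consist of chi-squared testing for the differences in proportions among the PC versus HBT study arms". Sample size calculation is consistent with this, sizing the trial "using two-sided test for differences in proportion".
- **Other uses of covariates.** Logistic models come next in Statistical analysis, for "exploring the result of the screening and the relation to various types of key study variables in addition to study arms". Site reappears under Subgroup analyses as a possible moderator. Gender is named for subgroup analysis under Aims and objectives.
- **Outcome.** A participant succeeds by being "fully up to date on all their needed screenings for these four health conditions (three for men"), in one yes/no variable.
- **Entry.** Inclusion criteria admit anyone overdue for at least one test, so men can enter needing 1 to 3 tests and women 1 to 4.
- **Baseline data.** The intake interview, held before randomisation, covers sociodemographic characteristics and "previous experiences with disease screening for each of our four conditions".

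**The concern.** The allocation scheme is built around site, and the test that decides the trial does not use it. Balancing arms within site removes between-site differences from the arm comparison. A crude chi-squared test still counts those differences in its variance, so its standard error is slightly too large whenever sites differ in uptake.

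The number of overdue tests is a second candidate. Success requires every needed test, so a participant needing one test and a participant needing four may face different hurdles. This count is known before randomisation, but the primary analysis does not use it.

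At stake is precision: the width of the confidence interval, and power if the true effect is smaller than planned. The validity of the trial is not at stake.

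**Working it through.** **1. The plan's own power figure.** Inputs from Sample size calculation: 450 per arm, 25% attrition (337 per arm left), a 15-point difference, two-sided α = 0.05. No control rate is given, so all rates from 1% to 85% were scanned. The least favourable is 42.5% versus 57.5%:

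- SE under the null = √(2 × 0.5 × 0.5 / 337) = 0.0385
- SE under the alternative = √(2 × 0.425 × 0.575 / 337) = 0.0381
- z = (0.15 − 1.96 × 0.0385) / 0.0381 = 1.96, so power = 97.5%

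Over 95% therefore holds at any control rate. At α = 0.0125 the minimum is 92.1%, consistent with the stated 90% for the individual tests.

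**2. Power with and without stratification.** The simulation used 4,000 trials per scenario. The size of 150 per arm per site is the reading under which 450 per arm and three sites agree. Covariate strength and the overall control rate of 40% are assumptions; the documents give neither. R² is the share of outcome variance explained by site, gender and number overdue together.

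- None: every site at 40%, R² = 0
- Moderate: site control rates 31/40/49%, R² about 0.08
- Strong: 25/39/56%, R² about 0.22
- Site only: 22/39/59%, R² about 0.09

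| True difference | Scenario | Crude chi-squared | CMH by site | CMH by site × gender × number overdue |
|---|---|---|---|---|
| 15 points | None | 99.4% | 99.4% | 99.3% |
| 15 points | Moderate | 99.5% | 99.5% | 99.7% |
| 15 points | Strong | 99.5% | 99.6% | 99.9% |
| 10 points | None | 84.6% | 84.6% | 84.5% |
| 10 points | Moderate | 86.2% | 87.1% | 88.7% |
| 10 points | Strong | 85.8% | 87.2% | 92.3% |
| 8 points | Moderate | 67.9% | 69.4% | 71.3% |
| 8 points | Strong | 67.5% | 70.5% | 77.8% |

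The site-only scenario gives crude versus site-stratified power of 86.8% versus 89.2% at 10 points and 69.1% versus 72.9% at 8 points. That puts the upper end for site alone nearer 4 points when site effects are strong and nothing else matters.

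**3. Type I error of the crude test.** With arms balanced within site, the true variance of the difference under the null is the nominal variance times (1 − R² for site). The actual error rate is then 2Φ(−1.96 / √(1 − R²)). R² for site is the between-site variance of the rates divided by 0.4 × 0.6 = 0.24:

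- Moderate: 0.0054 / 0.24 = 0.0225, giving 4.7% (simulated 4.4%)
- Strong: 0.0161 / 0.24 = 0.067, giving 4.2% (simulated 3.9%)
- Site only: 0.0229 / 0.24 = 0.095, giving 3.9% (simulated 3.4%)

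The simulated rates have a standard error of √(0.05 × 0.95 / 4000) = 0.34 points, so the formula is the steadier guide. Gender and number overdue are not balanced by design and add nothing to this conservatism; they matter only for precision.

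**4. As sample size.** Adjustment is worth roughly N / (1 − R²) participants. For N = 900, R² of 0.03, 0.08 or 0.20 equals about 28, 78 or 225 extra participants.

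**5. Losses counted as unscreened.** Suppose the 15 points applies to those followed up and 25% are lost in each arm. At a 60% control rate the intention-to-treat comparison becomes 0.75 × 60% = 45% versus 0.75 × 75% = 56.25%. With 450 per arm, crude power is 92.3%. Replacing 450 by 450 / (1 − R²) gives 94.2% for R² = 0.08 and 96.6% for R² = 0.20.

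**The case against.** The strongest reply is that the plan is internally consistent and valid. The trial is sized on an unadjusted comparison of proportions and analysed by one. Randomisation is of individuals within site, so omitting site cannot inflate type I error, and chance imbalance is already reflected in the standard error. At the planned effect almost nothing is lost. Every covariate strength above is assumed, and completion may be correlated across tests: most home tests share one visit, and one primary care contact covers all needed services. The count of overdue tests may then matter less than, say, needing the mailed stool test. All of this stands, and it limits the point to efficiency.

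The objection that such detail belongs in an analysis plan not shown here carries less weight. The article does not leave the primary test open. It names one, and although it never calls the test unstratified, that is the natural reading.

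A reader might infer more than the documents support:

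- **That the plan cannot deliver a percentage-point difference.** It tests differences in proportions and promises confidence intervals for proportions and for the primary outcome.
- **That the number of overdue tests is a major source of variance.** This is plausible from the outcome definition, but no figure shows it.
- **That covariates will be picked from observed baseline imbalances.** Statistical analysis says baseline differences will be examined, not that they decide the models.
- **That site and gender are otherwise unused.** Site is a planned moderator and gender a planned subgroup.

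**Conclusion.** The concern holds as a modest, inexpensive gain in efficiency. The stated primary test does not carry the randomisation strata into the analysis and sets aside baseline data that may be prognostic. It remains valid. If site is prognostic it is mildly conservative, with a type I error of about 4% to 4.7% under the assumed site effects.

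The power gain is under 1 point at 15 points. At 8 to 10 points it is roughly 1 to 3 points for site alone (nearer 4 in the site-only scenario at 8 points) and 2 to 10 points with gender and number overdue added. Without any association it is zero. In the moderate and strong scenarios most of the gain comes from gender and number overdue, so stratifying by site alone secures only the smaller part. These sizes rest on assumed covariate strengths and a 40% control rate. The direction does not depend on those particular values.

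**What to change.** Replace the primary-test sentence with one of these, chosen now:

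- a Cochran-Mantel-Haenszel test stratified by site, with the site-stratified risk difference and its 95% confidence interval; or
- a logistic model with arm, site, gender and baseline number of overdue tests, all pre-specified, reported as a marginal (standardised) risk difference with a 95% confidence interval.

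The first follows the randomisation with the fewest choices. The second can recover more precision if number overdue and gender prove prognostic. Keep the crude chi-squared test as a sensitivity analysis.

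The cost is one sentence and no new data, because every variable is known before randomisation. Trial status reports 705 of 900 enrolled in January 2020, so the change should be dated and fixed before any comparison of outcomes by arm.
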